# Effect of targeted vs standard fortification of breast milk on growth and development of preterm infants (≤ 32 weeks): study protocol for a randomized controlled trial

**DOI:** 10.1186/s13063-020-04841-x

**Published:** 2020-11-23

**Keywords:** Preterm, Very low birth weight, Enteral nutrition, Breast milk, Fortification, Growth

## Abstract

**Background:**

Human milk is recommended for all very low birth weight infants. Breastmilk is highly variable in nutrient content, failing to meet the nutritional demands of this group. Fortification of human milk is recommended to prevent extrauterine growth retardation and associated poor neurodevelopmental outcome. However, standard fortification with fixed dose multicomponent fortifier does not account for the variability in milk composition. Targeted fortification is a promising alternative and needs further investigation.

**Methods:**

This randomized controlled trial will recruit preterm infants (≤ 32 weeks of gestation) within the first 7 days of life. After reaching 80 ml/kg/day of enteral feeding, patients will be randomized to receive standard fortification (HMF, Nutricia) or targeted fortification (modular components: Bebilon Bialka, Nutricia—protein; Polycal, Nutricia—carbohydrates; Calogen, Nutricia—lipids). The intervention will continue until 37 weeks of post-conception age or hospital discharge. Parents and outcome assessors will be blinded to the intervention. The primary outcome measure is velocity of weight, length, and head growth until 36 weeks post-conceptional age or discharge. Secondary outcomes include neurodevelopment at 12 months assessed with Bayley Scale of Development III, repeated at 36 months; body composition at discharge and at 4 months; and incidence of necrotizing enterocolitis, sepsis, retinopathy of prematurity, and bronchopulmonary dysplasia.

**Discussion:**

Targeted fortification has previously been shown as doable in the neonatal intensive care unit context. If it shows to improve growth and neonatal outcome, choosing the targeted fortification as a first line nutritional approach in very low birth weight infants may become a recommendation.

**Trial registration:**

ClinicalTrials.govNCT03775785, Registered on July 2019.

## Administrative information

The order of the items has been modified to group similar items (see http://www.equator-network.org/reporting-guidelines/spirit-2013-statement-defining-standard-protocol-items-for-clinical-trials/).

## Introduction

### Background and rationale {6a}

#### Premature birth

About 15 million of infants are born premature (< 37 completed weeks of gestation) every year. Prematurity is a leading cause of death in newborns and (after pneumonia) in children up to 5 years of age. Children born premature suffer from long-term health consequences such as unfavourable cardiovascular and metabolic profile, and poorer neurological outcome [1].

In spite of a tremendous improvement in neonatal care during the last decade, nutrition in very premature infants still poses a challenge. The recommended nutritional intakes are often not achieved, and extrauterine growth restriction (EUGR) is common even in developed countries [2]. At achieving term-equivalent age, extremely preterm infants are lighter and shorter, and they have smaller head circumference and less favourable body composition compared to their term peers [3, 4]. Suboptimal nutritional intakes and postnatal growth restriction have long-term negative impact on growth and development and are associated with lower IQ scores at school age (Lucas [5]; Ehrenkranz et al. [6]).

Human milk is considered the best nutrition choice for all very low birth weight (VLBW) infants due to multiple benefits such as improved feeding tolerance, lower rates of necrotizing enterocolitis (NEC) and sepsis, reduced length of hospital stay, and, in a long perspective, improved neurodevelopment and lower risk for hypertension [7].

#### Fortification of human milk

Native human milk does not cover the high nutritional needs of VLBW, and so fortification of both own mother’s milk (OMM) and donor human milk (DHM) is recommended to prevent EUGR and the associated poor neurodevelopmental outcome [6, 8, 9]. Currently, there are three types of human milk fortification.

*Standard fortification* (SF) with a fixed dosage compound product is based on assumed nutrient content of OMM or DHM without accounting for nutrient concentrations in preterm human milk. Human milk however is highly variable in the nutrient content, both between the mothers and between the samples from the same mother [10, 11]. A recent study suggested that not taking this variability into account leads to inadequate intake in about 25–40% VLBW due to low content of protein and energy [12].

*Adjustable fortification* is based on supplementing naïve human milk with protein. This approach uses blood urea nitrogen (BUN) levels as a surrogate of metabolic response to the fortification. In a retrospective study, preterm infants receiving adjusted fortification had higher intakes of protein, better growth pace, and higher developmental scores at 18 months compared to infants on standard fortification [13].

*Tailored/targeted fortification* (TF) accounts for variability of native human milk content. Milk analysis is performed on regular basis to determine its macronutrient content. Based on the results, protein, fat, and carbohydrate are added to milk as modular products with the aim to achieve the recommended concentrations [14]. Feasibility and safety of TF was shown in a pilot study by Rochow et al. [12]. The same group conducted a trial including 157 VLBW, which showed that targeted fortification of human milk improved growth velocity (conference abstract/personal communication) [15]. Long-term effects of targeted fortification, such as neurodevelopment and body composition, remain to be studied.

The current randomized trial will compare targeted fortification with standard fortification (the method most commonly used in clinical practice) and its effect on growth, body composition, and development in premature infants born < 32 weeks of gestation.

### Objectives {7}

#### Research hypothesis

Tailored fortification of enteral nutrition improves weight gain velocity of preterm infants born at ≤ 32 weeks of gestation compared to standard fortification.

#### Study objectives

##### Primary objective

The primary objective is to determine if tailored compared to standard fortification of enteral nutrition improves weight gain velocity of preterm infants born at ≤ 32 weeks of gestation.

##### Secondary objectives

*Key secondary objectives*

The key secondary objectives are to determine the following anthropometric parameters in preterm infants born at ≤ 32 weeks of gestation at discharge and at 4 months:
Feeding toleranceVelocity of weight gainLength and head growthBody composition (by air displacement plethysmography, PeaPod)

*Other secondary objectives*
Neurodevelopmental outcome:
12 months corrected age: BSID-III (Bayley Scale of Development Third Edition)3.5 years of corrected age: BSID and WPSSI-IV (Wechsler Preschool and Primary Scale of Intelligence, Fourth Edition IV)Behavioural problems: parental assessment by CBCL (Child Behaviour Check List) at 3.5 years corrected ageTo compare the incidence of NEC, retinopathy of prematurity (ROP), and bronchopulmonary dysplasia (BPD) between both study groups

### Trial design {8}

The trial is designed as a randomized observer and patient blinded controlled multicentre superiority trial with two parallel groups with 1:1 allocation ratio.

## Methods: participants, interventions, and outcomes

### Study setting {9}

The study will be carried out in three different sites (2 separate neonatal departments within the Medical University of Warsaw, and the Neonatal Department of the Wroclaw Medical University). All study sites are level III teaching hospital with approximately 2500–3000 (100 ≤ 32 weeks of gestation) deliveries per year. The local protocol is based on standard fortification of OMM and DHM. However, the staff is willing to implement new procedures in order to improve neonatal outcome. This should improve trial recruitment and adherence. The current OMM feeding rate during hospital stay in infants born at < 32 gestational age (GA) is 80%.

### Eligibility criteria {10}

All parents of infants born at less than 32 weeks of GA and admitted to the participating units will be approached by one of the research team members within the first week of life (as full enteral feeding is usually reached at a minimum of 7 days of life). Recruitment will take place between June 2019 and December 2021. After obtaining written consent for participating in the trial, the patient’s medical record number (MRN) will be immediately registered on a secure web-based platform and demographic data will be recorded.

#### Inclusion criteria

Patients eligible for the trial must comply with all of the following at randomization:
Gestational age at birth ≤32 weeksEnteral feeding of at least 80 ml/kg/day50% donor or maternal milk-based enteral feedingParenteral/legal guardian consent

#### Exclusion criteria

Formula feedingSmall for gestational age (birth weight < 3rd percentile)Presence of congenital abnormalities, which increase the risk of NECNECWithdrawal of feeding > 7 daysSepsisDeath

### Who will take informed consent? {26a}

All parents of infants born at less than 32 weeks of gestation and admitted to one of the study sites will be approached by one of the research team members within the first 7 days of life. He/she will provide oral and written information about the study. Parents of the patient will then be able to have an informed discussion with the attending physician and/or study personnel. Research team members will obtain written consent from the parents willing to participate in the trial. Information consent forms and information sheets will only be provided in Polish for all parents. Given the limited diversity of our population, we will not recruit newborns of foreign parents unless they speak Polish on a level allowing full understanding of the study conduct.

### Additional consent provisions for collection and use of participant data and biological specimens {26b}

We do not plan to collect samples for ancillary studies.

### Interventions

#### Explanation for the choice of comparators {6b}

SF is based on the assumption that all human milk has a protein level of 1.5 g/dl. Human milk however is highly variable in the nutrient content, both between the mothers and between the samples from the same mother [10, 11]. A recent study suggested that not taking this variability into account leads to inadequate intake in about 25–40% VLBW due to low content of protein and energy [12]. Nonetheless, it is the most widely used strategy for human milk fortification, and thus, its choice as a comparator is logical.

#### Intervention description {11a}

After reaching 80 ml/kg/day of enteral feeding, patients will be randomized to receive SF (Bebilon HMF, Nutricia) or TF (protein: Bebilon Suplement Bialka, Nutricia; lipids: Calogen, Nutricia; carbohydrates: Polycal, Nutricia) (Fig. 1). The content of macro- and micronutrients of each product is given in Table 1.

**Fig. 1 Fig1:**
[figure not shown]
Algorithm for tailored enteral nutrition. *Additional amount of fat, protein, and/or carbohydrate required to achieve target levels of macronutrients will be calculated as addition = ESPGHAN recommendations (OMM/HDM + increment by routine fortification). **One-to-one CLC support, followed by weekly lactation re-evaluation. If OMM amount is less than 20 ml/day for ethical reasons, it will not be submitted for analysis and fortification will be continued as per most recent report. *To enhance feeding tolerance at the start of the intervention, TF will be gradually introduced in a stepwise manner over a 3-day period (maximum target dosage of added fat, protein, and carbohydrate at day 1 was 0.3 g, day 2 was 0.6 g, and day 3 was 0.9 g per 100 ml breast milk), as suggested by Rochow*^*2*^*. On day 4, the full amount of TF for each macronutrient will be prescribed; this day will be marked the starting point of the intervention period. Feeding route and quantity advancement will comply with standard unit protocol*

**Table 1 Tab1:** Content of the products used as standard fortification (ST) and tailored fortification (TF)

**Standard fortification**					
**Bebilon HMF (Nutricia) *1 sachet (2.2 g) per 50 ml HM**	**Energy (kcal/100 g)**	**Protein (g/100 g)**	**Carbohydrates (g/100 g)**	**Fat (g/100 g)**	**Osmolality (mmol/l)**
	347	25.2 *- Whey and casein hydrolysate (of cow’s milk)*	62.2 *- Lactose, 0.4* *- Polysaccharide, 51.6*	0	399
	**Minerals (per 100 g)**			**Vitamins (per 100 g)**	
	Natrium, 803 mg; potassium, 528 mg; chloride, 573 mg; calcium, 1491 mg; phosphate, 872 mg; magnesium, 115 mg; zinc, 14 mg; cuprum, 803 μg; manganum, 183 μg; selenium, 39 μg; iodine, 252 μg			A, 5275 μg; D, 115 μg; E, 60 mgα-TE; K, 144 μg; B1, 3005 μg; B2, 3922 μg; B3, 59 mgNE; pantothenic acid, 17,201 μg; B6, 2523 μg; folic acid, 688 μg; B12, 4.6 μg; biotin, 57 μg; C, 275 mg	
**Tailored fortification**					
	**Energy**	**Protein**	**Carbohydrates**	**Fat**	**Minerals (per 100 g)**
**Bebilon Suplement Bialka (Nutricia); protein supplement**	338 kcal/100 g	82.1 g/100 g *- Whey and casein hydrolysate (of cow’s milk)*	2.2 g/100 g - Lactose, 1.3 g/100 g	0.1 g/100 g *- Saturates, 0.1 g/100 g*	Natrium, 776 mg; potassium, 1226 mg; chloride, 66 mg; calcium, 524 mg; phosphate, 516 mg; magnesium, 46 mg; manganum, 210 μg; selenium, 27 μg
**Polycal (Nutricia)**	384 kcal/100 g (1 scoop = 5 g = 19 kcal)	0	- Maltodextrin - Lactose, < 30 mg/100 g	0	0
**Calogen Neutral (Nutricia)**	450 kcal/100 ml	0	0.1 g/100 ml	Total, 50 g/100 ml *- Saturates, 5.3 g/100 ml* *- Monounsat, 30.4 g/100 ml* *- Polyunsat, 14.3 g/100 ml* *- Ration Ω6/Ω3, 5.1*	0

*Monounsat* manosaturates, *Polysat* polysaturates

Milk fortification is routinely done twice a day (at 8 am and at 8 pm) for each following 12-h nursing shift (Fig. 1). For the purpose of the study, TF will be integrated in this schedule and performed by experienced registered nurses.

An experienced laboratory technician will perform milk analysis in the neonatal intensive care unit (NICU) research laboratory at Princess Anna Mazowiecka Hospital thrice per week at 10:00 am (Monday/Wednesday/Friday) from batches collected from the two previous days. A 10-ml aliquot from each batch of native breast milk will be used for macronutrient analysis (Miris® HMA) as per protocol (Fig. 1). The remaining batch will first be fortified with the routine fortifier. Macronutrient analysis will determine how much extra fat, protein, or carbohydrate is needed in the batch to obtain final target fortified breast milk (FBM).

Milk samples from other sites will be delivered by medical transport in secure freezing containers at 8:00 am. The mean of three measurements per batch (3 × 2–3 ml) will be used to calculate the required amount of extra fat, protein, and carbohydrate for the following 3 days of fortification using a predefined Excel spreadsheet (Microsoft Inc., Redmond, Washington). Milk analysis will be performed in both treatment arms; however, only the intervention group will receive TF. Results, together with required amounts of macronutrients, will be emailed to the participating centres before noon the same day.

The desired macronutrient concentration in breast milk will be 4.4 g/100 ml of fat, 3 g/100 ml of protein, and 8.8 g/100 ml of carbohydrate in order to meet the European Society for Paediatric Gastroenterology, Hepatology, and Nutrition (ESPGHAN) guidelines (6.6 g/kg/day of fat, 4.5 g/kg/day of protein, and 13.2 g/kg/day of carbohydrate) assuming an intake of 150 ml/kg/day.

Target fortification (TF) will be done in 3 steps:
Determination of macronutrient concentration in own OMM/HDMSF: human milk fortifier, HMF NutriciaTF: adding fat, protein, and/or carbohydrate to achieve target levels of macronutrients

In cases where a macronutrient component after SF will exceed the target value, only the other deficient macronutrient components will be adjusted.

To enhance feeding tolerance at the start of the intervention, TF will be gradually introduced in a stepwise manner over a 3-day period (maximum target dosage of added fat, protein, and carbohydrate will be as follows: at day 1, 0.3 g; day 2, 0.6 g; and day 3, 0.9 g per 100 ml breast milk), as suggested by Rochow et al. [12]. On day 4, the full amount of target fortification for each macronutrient will be prescribed; this day will be marked the starting point of the intervention period. Patients will be fed every 3 h via a gastric tube by registered nurses. Starting from 33 weeks of post-conceptional age (PCA), non-nutritive sucking stimulation will be initiated by occupational therapists. At approximately 34 weeks of PCA, infants will be transitioned to bottle feeding. When breastfeeding is established, patients will receive TF as one or two bottle feeds.

As a safety assessment to ensure that an appropriate amount of fortifier is added, osmolality of unfortified and FBM samples will be measured 3320 with the use of Micro-Osmometer; Advance Instruments, Norwood, MA. Bedside nurses will be then informed whether the osmolality of FBM is within the acceptable target range (400–480 mOsmol/kg) before the milk administered during the next 12-h shift. Osmolality lower or higher than the defined target range will be considered as a sample preparation error of fortification, and a new batch of breast milk will be prepared. Prescription of TF will be completed before noon. The attending physician will then approve these prescriptions. Subsequently, individual additives will be provided by nutrition services. Bedside nurses will prepare batches of FBM including the additives for target fortification and divide it into single feeding portions to be given to infants. Blood urea nitrogen will be used as a surrogate for protein nutriture and will be monitored weekly [16].

The intervention will continue until 37 weeks of post-conception age or hospital discharge. Parents, attending physicians, and outcome assessors will be blinded to the intervention.

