#### Relevant concomitant care permitted or prohibited during the trial {11d}

Participants should continue to receive standard neonatal care. Interventions aimed at improving weight gain such as increased daily intake (> 160–170 ml/kg/day) or increased dosing of vitamin D (> 1000 IU/l) or prescription of milk formula will be forbidden.

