#### Implementation {16c}

A member [a physician not involved in the patients care] of the research team will prescribe the allocated fortification on the patient’s drug chart. Milk fortification is routinely done twice a day (at 8 am and at 8 pm) for each following 12-h nursing shift (Fig. 1). For the purpose of the study, TF will be integrated in this schedule and performed by experienced registered nurses (RNs). The intervention will be performed by a RN blinded to treatment allocation. Patient’s data along with the result of the allocation will be sent to the statistical team. The randomization list will remain with the statistical team for the whole duration of the study.

All randomized infants who are prematurely discontinued from study will be considered *off study intervention/on study* and will follow the same schedule of events as those infants who continue study treatment. All of these infants will be followed through 36 months as scheduled. Once an infant is enrolled or randomized, the study site will make every reasonable effort to follow the infant for the entire study period. Participants may withdraw from the study for any reason at any time.

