### Assignment of interventions: blinding

#### Who will be blinded {17a}

The bedside nurse, treating physicians, clinical psychologist, and data analysts will be blinded to the treatment allocation. Milk fortification will be performed in the milk bank by an experienced RN. Prepared milk portions will be transported to unit. Feeding portions from both treating arms will not differ in colour and structure.

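### The email of milk-analysis results and required additions is not limited by arm or recipient, so the plan does not prevent carers from seeing control infants' measured shortfalls

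*Protocol article*

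**What the plan says.** All statements are in the protocol article.

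- **Analysis and calculation** (Intervention description {11a}, text after Table 1). The mean of three measurements per batch "will be used to calculate the required amount of extra fat, protein, and carbohydrate for the following 3 days of fortification". The next sentence reads: "Milk analysis will be performed in both treatment arms; however, only the intervention group will receive TF".
- **Release** (same paragraph). "Results, together with required amounts of macronutrients, will be emailed to the participating centres before noon the same day". No arm and no recipient role is named.
- **Approval and preparation** (end of the same section). On the TF prescriptions: "The attending physician will then approve these prescriptions". Nutrition services then supply the additives, and "Bedside nurses will prepare batches of FBM including the additives for target fortification". The section closes by listing attending physicians among those blinded.
- **Prescribing** (Implementation {16c}). "A member [a physician not involved in the patients care] of the research team will prescribe the allocated fortification". This section also says that the nurse who performs the intervention is blinded.
- **Blinding** (Who will be blinded {17a}). The bedside nurse and treating physicians are blinded, and "Milk fortification will be performed in the milk bank by an experienced RN".
- **Concomitant care** ({11d}). "Interventions aimed at improving weight gain such as increased daily intake" are forbidden. The examples given are feed volume, vitamin D and formula.

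**The concern.** The comparator is a fixed-dose product given without acting on the measured content of the milk. The trial nevertheless measures that content for control infants, on a thrice-weekly schedule, and describes a message to the centres that is not confined to the TF arm. A carer who knows that a control infant's milk is short of protein or energy may feed or manage that infant differently, within what the protocol allows. A carer who sees required additions for some infants and not for others may work out the allocation.

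Two things are at stake. The first is the contrast between arms: any partial correction of control infants shrinks the growth difference that the superiority design (Trial design {8}) is meant to detect. The second is the blinding of the staff who feed, weigh and manage the infants. The statistical methods section {20a} separately names a one-tailed noninferiority test for the primary outcome. If that test were used, the same drift would make the arms look alike and favour a positive conclusion.

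**Working it through.** **Step 1. The statements side by side.**

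| Question | Statement A | Statement B |
|---|---|---|
| Whose milk is analysed? | Both arms ({11a}) | – |
| For whom are additions calculated? | Per batch, no arm named ({11a}) | Only the intervention group receives TF ({11a}) |
| Who gets the email? | Participating centres, no role named ({11a}) | – |
| Who handles the prescription? | Attending physician approves TF prescriptions ({11a}) | Physician outside the infant's care prescribes ({16c}); attending and treating physicians blinded ({11a}, {17a}) |
| Who adds the products? | Bedside nurses ({11a}) | Nurse in the milk bank ({17a}); bedside nurse blinded ({17a}); performing nurse blinded ({16c}) |

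The sentence restricting TF to the intervention group governs what is given. It does not say what is calculated, sent or seen. The sentence on email comes directly after it and carries no restriction of its own. If only the prescriber of {16c} received the message, the route would be closed, but {11a} does not say so. Its approval and preparation steps also put two blinded roles into the handling chain.

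**Step 2. Size, as an illustration only.** The plan states no contamination rate, so there is no figure of the plan to reproduce on this point.

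Inputs from Sample size {14}: difference 1.9 g/kg/day, SD 3.75, alpha 5% two-sided, 91 infants per group. The 91 comes from the Bayley-III calculation and does reproduce: 2 × (1.960 + 0.842)² × 12² / 5² = 90.4, rounded up to 91.

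Assumption: contamination reduces the mean difference by a share c, so the difference becomes 1.9 × (1 − c). If c is read as a share of control infants, each of them gets the whole TF effect.

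Standard error: 3.75 × √(2/91) = 0.556. Power ≈ Φ(difference / 0.556 − 1.96).

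| c (assumed) | Difference | Difference / SE | Power, weight gain |
|---|---|---|---|
| 0 | 1.90 | 3.42 | 92.8% |
| 10% | 1.71 | 3.08 | 86.8% |
| 20% | 1.52 | 2.73 | 78.1% |
| 30% | 1.33 | 2.39 | 66.7% |

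Power of 80% needs a difference of about (1.960 + 0.842) × 0.556 = 1.56, so it is reached at c = 1 − 1.56/1.9, about 18%.

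The Bayley-III comparison (5 points, SD 12, 91 per group) has no such reserve. The same dilution gives 80.3%, 71.6%, 61.4% and 50.3%.

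**Step 3. Sensitivity to sample size.** Recruiting 200 and losing 10% leaves 90 per arm. A t test then gives 92.2% with no dilution and 86.0% with 10%, practically the same. Recruitment {15} speaks instead of 200 valid observations in every arm, which conflicts with {14} and is a separate matter. At that size the standard error is 0.375, and even 20% dilution leaves Φ(1.52/0.375 − 1.96), about 98%.

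**The case against.** A reader might infer that treating staff are sent a written deficit and its correction for every control infant. The documents do not support that.

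- The required amount is the TF addition, and the sentence before the email limits TF to the intervention group. On one natural reading, a control infant has no required amount to send.
- The centres need not mean the infant's carers. The prescriber in {16c} is outside the infant's care, and TF prescriptions are due before noon, as is the email. That fits a message to that prescriber.
- Giving modular products to a control infant would break {11a} and {16c}. The ban in {11d} is worded as non-exhaustive, so it plausibly covers such additions even though they are not among its examples.
- Standard fortification is defined by not acting on milk content. Measuring it in both arms is compatible with the comparator.
- The dilution model assumes the full TF effect for a share of controls. Influence within permitted feeding would probably produce less, and no source gives c.
- Email lists are operational detail that an article may leave to the full protocol.

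The first five points stand, and they reduce the matter to an open risk. The last stands only in part. A missing distribution list would not be a finding, but here the article does state the data flow, states it without restriction, and describes approval and preparation steps that conflict with its own blinding statements. Those conflicts are in the text and do not depend on what the full protocol adds.

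**Conclusion.** The point holds as a gap in safeguards. The plan does not prevent carers from seeing control infants' measured shortfalls, because the release of results is limited by neither arm nor recipient, and because two roles described as blinded also approve TF prescriptions or add the products. Whether control figures actually reach carers, and whether care would change, cannot be determined from the article.

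The power figures are a range under an assumed dilution, not an estimate. With 91 per arm, the weight-gain comparison tolerates up to about 18% dilution before power falls below 80%, whereas the Bayley-III comparison falls below 80% with almost any dilution. It would be wrong to conclude that the trial is underpowered for weight gain on this account. The change is worth making because it costs little and protects both the contrast and the blinding.

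**What to change.** 1. In Intervention description {11a}, state that required additions are calculated and released for TF infants only, and only to the prescriber outside the infant's care ({16c}) and the person who prepares the milk in the milk bank ({17a}).
2. State that control-arm analysis results go into the database without calculated additions and are not released to the centres before the primary analysis.
3. Reconcile {11a}, {16c} and {17a} on who prescribes, who approves, who prepares the milk and which of these roles is blinded. Any role that keeps sight of TF prescriptions or additives should not be listed as blinded.

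The cost is a re-routed email list and restricted database access, with no extra staff or tests. The downside is that the preparer of TF milk is openly unblinded, and {16c}, which now describes the performing nurse as blinded, must say so.

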### Assignment of interventions: allocation

#### Sequence generation {16a}

The allocation sequence will be computer-generated by a statistical team member who will inform the researchers about the designated study group. Block randomization with stratification by delivery mode will be implemented. Patients will be randomly assigned to standard or tailored enteral nutrition fortification in 1:1 ratio. The block size will be variable and concealed until primary endpoint analyses.

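### Attending physicians and bedside nurses are called blinded, but the described workflow has them approve and mix a treatment given in one arm only

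*Protocol article*

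**What the plan says.** Two sections claim blinding of care staff. The end of Intervention description {11a} states: "Parents, attending physicians, and outcome assessors will be blinded to the intervention". Who will be blinded {17a} states: "The bedside nurse, treating physicians, clinical psychologist, and data analysts will be blinded to the treatment allocation".

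The workflow is spread over three sections:

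- **Who receives targeted fortification ({11a}).** "Milk analysis will be performed in both treatment arms; however, only the intervention group will receive TF".
- **Who approves it ({11a}).** After the prescription is completed: "The attending physician will then approve these prescriptions".
- **Who mixes it ({11a}).** "Bedside nurses will prepare batches of FBM including the additives for target fortification".
- **Who mixes it ({17a}).** "Milk fortification will be performed in the milk bank by an experienced RN". This section adds that the portions look alike in both arms.
- **Who prescribes it (Implementation {16c}).** A physician not involved in the infant's care "will prescribe the allocated fortification on the patient’s drug chart". The same paragraph says that the registered nurse performing the intervention is blinded.

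Trial design {8} describes the trial as observer and patient blinded. The Abstract claims blinding only for parents and outcome assessors.

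**The concern.** Both arms start from the routine fortifier. The targeted arm then receives modular protein, fat or carbohydrate according to the milk analysis. No sham additive is described for the control arm. Anyone who approves a targeted prescription, or adds the modular products, therefore knows the arm, and {11a} gives these two tasks to the two staff groups that are called blinded.

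Care staff who know the arm could, even without intending to, manage feeding differently or judge feeding tolerance differently. Poor tolerance is a criterion for discontinuing the intervention in {11b}, and feeding tolerance is both an efficacy and a harm outcome in Outcomes {12}. If the trial report repeats the {17a} statement, readers would credit a protection against performance bias that the described conduct does not provide.

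**Working it through.** No arithmetic applies, because the plan states no figure on this point. The check compares, for each role, what is claimed with what is described.

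**Attending or treating physician**
- Claim: blinded ({11a} and {17a}).
- Workflow: approves the targeted prescriptions ({11a}), which exist in one arm only ({11a}).
- Reasoning: an infant whose prescription comes for approval is in the targeted arm, and an infant for whom none comes is, by elimination, in the standard arm. The uninvolved prescriber in {16c} would protect the blind alone, but the later approval by the attending physician undoes this. The unblinding procedure in {17b} discloses the allocation to the treating physician, so it presupposes that this physician does not already know it.
- Result: direct contradiction, partly within {11a} itself.

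**Bedside nurse**
- Claim: blinded ({17a}).
- Workflow: prepares batches with the targeted additives ({11a}); alternatively, a nurse in the milk bank does so ({17a}).
- Reasoning: the two sections name different people and places. Under the {11a} version the bedside nurse knows the arm. Under the {17a} version the bedside nurse can be blind, because the portions look alike.
- Result: direct contradiction. The claim holds only if the {17a} version is followed.

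**Nurse who performs the fortification**
- Claim: blinded ({16c}).
- Workflow: adds modular components in one arm only.
- Reasoning: similar-looking portions protect those who receive or give the milk, not the person who makes it up.
- Result: the claim cannot hold as written, wherever mixing takes place.

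**Chart entry**
- Workflow: the allocated fortification is written on the infant's drug chart ({16c}).
- Reasoning: the document does not say who reads the chart, so this is a likely route to unblinding, not a shown one.

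**Parents, psychologist and outcome assessors**
- Claim: blinded (Abstract, {8}, {11a} and {17a}).
- Workflow: none of the steps above is assigned to them.
- Result: not directly contradicted.

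**Where knowledge of the arm could act.** Registered nurses give the tube feeds ({11a}). Poor tolerance leads to discontinuation ({11b}), and tolerance is also an outcome ({12}). The document does not name who judges tolerance. That care staff do so is a reasonable assumption, but it remains one.

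**The case against.** **What stands on the other side.** Weight is measured objectively. The weight outcome is a rate, so a later end date does not mechanically increase it. Feeding advancement follows the unit protocol (legend to Fig. 1), {11d} forbids intake increased beyond 160–170 ml/kg/day and formula, and the {11b} tolerance criteria carry numerical thresholds. Discontinued infants stay on study and in the intention-to-treat analysis. These safeguards limit the scope for bias but do not make the blinding statement true.

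**Stronger readings that the document does not support.**

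- *The data analysts are unblinded.* A reader might infer this because the sequence is "computer-generated by a statistical team member who will inform the researchers about the designated study group", and because the statistical team receives patient data with the allocation and keeps the list throughout. But the list-holder and the analysts called blinded in {17a} may be different people. No breach is shown; the separation is simply not stated.
- *Unblinded clinicians set the end of the growth window.* The Abstract and Outcomes {12} let discharge close the window, but Plans for assessment {18a} ends weight gain velocity at 4 weeks. The inconsistent window is a separate matter.
- *Unblinded care staff attribute serious adverse events.* The harms section {22} gives that judgement to the investigators, without saying that these are the treating staff.
- *The trial is open-label but labelled as blinded.* The label in {8} covers observers and patients. What fails is the added claim about care staff.

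**Size.** The effect sought, 1.9 on 19.3 g/kg/day (1.9/19.3 = 9.8%), is the planned difference and says nothing about bias. Any false-positive rate would need an invented bias, so none is given.

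**Condensation.** A fuller protocol may add detail, but the article states both versions and a site cannot follow both.

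**Conclusion.** The point holds for attending physicians, bedside nurses and the nurse who performs the fortification. Followed as written, the plan does not deliver the blinding of care staff stated in {11a}, {16c} and {17a}.

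Under {11a}, every targeted prescription goes through the attending physician, so up to every infant in that arm is affected. The size of any resulting bias cannot be computed from the document. It would act through feeding management and the judgement of tolerance, on the assumption that care staff make those judgements.

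The conclusion rests on two readings: that the prescriptions the physician approves are the targeted ones, as the preceding sentence in {11a} says, and that no sham additive is used in the control arm, since none is described. The separation of list-holder and analyst needs clarifying but is not a shown failure.

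**What to change.** Reconcile {11a}, {16c} and {17a} so that each step that reveals the allocation stays with staff outside the infant's care and outcome measurement:

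1. **Approval.** Assign approval of the targeted prescription to the uninvolved physician already named in {16c}. Whether this leaves adequate clinical oversight is for the sponsor to settle.
2. **Mixing.** Keep one description, the milk-bank nurse in {17a}, remove the bedside-nurse version from {11a}, and acknowledge the mixing nurse as unblinded.
3. **Chart.** Use the same neutral order in both arms, identified by study number.
4. **Osmolality result.** State whether the check reported to bedside nurses in {11a} is made in both arms, since a report in one arm only would reveal it.
5. **Analysis.** State that the holder of the randomization list is not the blinded analyst, who receives coded arms.

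The article does not say that each of the three sites has a milk bank. Where a site cannot work this way, describe its physicians and nurses as unblinded and the trial there as blinded for parents and outcome assessors only, which is all that the Abstract claims. Recruitment began on 1 June 2019, and a later change cannot restore blinding. The same description is therefore needed for infants already treated under the {11a} workflow.

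The cost is a small workflow change that uses roles already in the protocol, and less visibility of milk composition at the bedside. The unblinding procedure in {17b} remains available when a treating physician needs the allocation.
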